## 1711 **16.7 Outcome definitions**

- 1712     ▪ The primary endpoint is the international normalized ratio (INR) at hospital arrival.
- 1713     ▪ Secondary outcomes (prehospital and hospital phases)
- 1714     ▪ The delta-INR value between the prehospital INR and the INR at hospital arrival. The Point of
- 1715     Care Device Coaguchek® will measure these two INR values
- 1716     ▪ The change in fibrinogen between the fibrinogen on hospital admission and the fibrinogen
- 1717     initially collected in the prehospital setting.
- 1718     ▪ Number of RBCs, platelet concentrates, fibrinogen, coagulation factors, plasma, administered in
- 1719     the first 24 and 48 hours.
- 1720     ▪ The total length of stay in intensive care
- 1721     ▪ Survival in the first 30 days.
- 1722     ▪ Collection of technical and logistical difficulties encountered before, during and after the
- 1723     administration of FLYP.

1724

1725

## 1726 **Analysis methods**

### 1727 **First endpoint**

- 1728     ▪ For the primary outcome analysis, INR at hospital admission will be considered to have been
- 1729     performed at a comparable time in each patient and will be compared across the two arms with
- 1730     the Mann–Whitney U test. If the initial characteristics of patients are unbalanced between the
- 1731     two groups after randomization, an adjusted analysis will be considered with a regression
- 1732     method. When appropriate, both adjusted and unadjusted results will be reported.

1733

### 1734 **Secondary endpoints**

- 1735     ▪ Comparison of fibrinogen changes by group: paired t-test, analysis of covariance
- 1736     ▪ Comparison of the volumes of blood loss, volumes infused or transfused, the quantity of amines
- 1737     used between the two groups (Chi2, Fisher's exact, Student's, Mann-Whitney tests).
- 1738     ▪ Comparison of the INR differential, delta INR : [INR at hospital admission - initial INR at the
- 1739     point of injury] between the two groups

- 1740                   ▪ We will compare the Delta-INR values between the plasma and control groups using a
- 1741                   linear mixed model with an independent covariance matrix, considering study group, time, and
- 1742                   Injury Severity Score levels as fixed effects and incorporating a random intercept.
- 1743                   ▪ Comparison of the length of stay in intensive care between the 2 groups : Student's t test, Mann-
- 1744                   Whitney test.
- 1745                   ▪ Number of days of hospitalization: Student's t-test, Mann-Whitney test
- 1746                   ▪ Survival analysis over the first 30 days: Kaplan Meier graphic, log-rank test.
- 1747                   ▪ Feasibility endpoint : listing of technical and logistical difficulties in plasma administration ,
- 1748                   number ad percentage of patients, number and percentage of plasma vials.
- 1749                   ▪ The analysis will all take into account a possible center effect.
- 1750                   ▪ Safety Endpoint is the occurrence of any of the following adverse events: thrombosis, allergic
- 1751                   symptoms, transfusion-related acute lung injury, and transfusion-associated circulatory
- 1752                   overload. The traceability of plasma, including prescription, delivery, and follow-up
- 1753                   procedures, will be assessed using the plasma follow-up sheet from the French Military Blood
- 1754                   Institute. The Health Defence Service will realize the qualitative and quantitative analysis of
- 1755                   Adverse Events. There is no formal statistical test preplanned
- 1756                   ▪ If the initial characteristics of patients are unbalanced between the two groups after
- 1757                   randomization, an adjusted analysis will be considered with a regression method. Where

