### **Secondary endpoints:**

- The delta-INR value between the prehospital INR and the INR at hospital arrival. The Point of Care Device Coaguchek® will measure these two INR values
- Listing of technical and logistical difficulties encountered before, during, and after the administration of FLYP.
- The change in fibrinogen level between hospital admission and prehospital setting. The number of RBC units, platelet units, fibrinogen, plasma units, and quantity of coagulation factors administered during the first 24 and 48 hours.
- Length of stay in intensive care
- Length of hospitalization
- 30-days survival.

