### 3.3.2 Hospital phase

#### At hospital arrival:

- Biological samples ( PT, aPTT., fibrinogen, CRP, and coagulation factors)
- Administration of the usual treatments.
- Follow-up by the hospital-based investigator for 30 days (
  - patient status (alive, deceased)
  - date of discharge from the intensive care unit and the hospital
  - follow-up of AEs, SAEs
  - Hemostasis test results collection.

All procedures performed during this phase will conform with the standard practices in use in each hospital.

Biological samples will not be stored after their usual processing.

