### **Data Analysis for the Secondary Endpoints:**

- The prehospital INR delta [between INR- management at the procedure site and INR-on arrival at the hospital] between the two groups will be studied with multilevel logistic regression modeling that will be fitted using a generalized estimating equation method to take into account time and both patient and hospital clustering. Where appropriate, this regression might be adjusted for unbalanced variables.
- The mean difference in fibrinogen levels between the two groups will be compared by a GEE model in the same way as for INR.
- The transfusion requirement will be compared by the number of blood products and plasma units transfused after arrival at the hospital, including packed RBCs, platelet concentrates, fibrinogen, coagulation factors, and Fresh frozen plasma. The transfusion requirement will be assessed at 6 and 24 h, taking the investigating center into account as a stratifying variable.
- The comparison of the median number of RBCs transfused between the two groups will use the Mann–Whitney U test
- The median number of days in the intensive care unit between the two groups will be studied overall and among surviving patients. They will be compared between the two groups by a Mann–Whitney U test.
- For each arm, actuarial survival will be visualized using the Kaplan–Meier estimator and compared with the log-rank test to estimate the effect of FLYP on survival. A multivariable Cox proportional hazard regression model may be fitted in cases of potential imbalance.
- The feasibility of administering FLYP will be judged by the responses to the CRF. page 9
- (Rate of positive responses to the various items)
- Safety outcome: The adverse event incidence will be compared between the two groups, using a Chi2 or a Fisher exact test.
- Exploratory subgroup analysis: we will report the effect size on the INR value in subgroups defined by variables of interest such as the type of injury, the prehospital vasopressor use, the prehospital intubation, the presence of a brain injury.
- Post-hoc analyses to further explain the primary outcome.  
We will measure, with an adapted model, the relationship between the INR value and the ratio of plasma-to-crystalloid volume, which seems to be an indicator of plasma dilution by superadded serum

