### **8.2 Anticipated number of people to be included in the research with its statistical justification and anticipated number of people in each research location**

- The recent literature  reports a coagulopathy rate of 50% of severely injured patients on arrival at the hospital.
- We determined that a sample size of 30 patients with coagulopathy in each group was adequate to detect a mean difference of 0.3 in INR values at hospital admission, assuming a standard deviation of 0.4, with a two-sided type I error of 0.05 and a power of 80%.

We chose this 0.3 anticipated effect size pragmatically, based on clinical judgment and the results of one previous observational study  in patients with traumatic hemorrhage of “before-after” FLYP administration

with Prothrombin Time (PT) as the endpoint, showed a significant improvement in PT “after” FLYP. A total of 124 patients were required to observe a statistically significant difference.

Assuming an incidence of coagulopathy of 50%, this resulted in 60 subjects per group. Given the a priori loss of 10% due to lack of informed consent, we rounded the target size of each group to 70 and included a total of 140 patients. To consider a median difference of 0.3 in INR values instead of mean difference, the sample size needs to be approximately 25 coagulopathic patients per group, for a total of 120 patients, based on the same alpha and beta risk assumptions. INR values will be presented according to their median (IQR) and by a three-category variable with cutoff values of 1.2 and 1.5.

[figure not shown]

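### Delta-INR and fibrinogen change are given different methods in the synopsis, protocol 8.1 and SAP 16.7; some do not suit a between-arm comparison of change, and the delta-INR mixed model is incompletely specified

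*Combined protocol and SAP*

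**What the plan says.** **Delta-INR.**
- The synopsis (statistical analysis) names generalized estimating equations (GEE) and gives no link or distribution.
- Protocol 8.1 says that delta-INR "will be studied with multilevel logistic regression modeling that will be fitted using a generalized estimating equation method", to allow for time and for clustering by patient and hospital.
- SAP 16.7 sets out to compare delta-INR values between the arms with a "linear mixed model with an independent covariance matrix, considering study group, time, and" ISS as fixed effects, plus a random intercept. No group-by-time term is listed. The level of the intercept (patient or centre) and the meaning of time are not stated.

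**Fibrinogen.**
- The synopsis compares medians at hospital admission.
- Protocol 8.1 uses GEE, handled as for INR.
- SAP 16.7 reads: "Comparison of fibrinogen changes by group: paired t-test, analysis of covariance".

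**How INR is measured.** Protocol 3.1 and SAP 16.7 say that the point-of-care device "will measure these two INR values". Protocol 3.3.1 describes the device test before treatment. The arrival samples in 3.3.2 are prothrombin time, aPTT, "fibrinogen, CRP, and coagulation factors", and no device test is mentioned. The schedule in 3.3.5 ticks PT/INR both prehospital and at admission, but its separate prehospital INR row only in the prehospital column.

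Protocol 8.1 refers to a separate complete analysis plan. No section says which text prevails when they differ.

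**The concern.** The question for both endpoints is whether the change from scene to hospital differs between FLYP and control. A logistic model needs a binary outcome, and none is defined for delta-INR. The cutoffs of 1.2 and 1.5 in protocol 8.2 apply to INR itself, and the SAP's general intention to categorise non-normal variables gives no cutoff for delta. A paired t-test asks whether patients changed, not whether the arms differ. A mixed model with group and time but no product of the two does not isolate the difference in change when it is fitted to repeated INR values.

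Delta-INR was the primary endpoint until the amendment dated 07/12/2019, so readers will look at it closely. With three unreconciled methods, the model could be chosen after the data are seen. Some of the choices would give a diluted estimate or none of the required contrast.

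**Working it through.** **1. The plan's own figure.** Protocol 8.2 calls 30 coagulopathic patients per arm "adequate to detect a mean difference of 0.3 in INR values at hospital admission". Its other inputs are SD 0.4, two-sided alpha 0.05 and 80% power.

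- n per group = 2(1.96 + 0.8416)² × 0.4² / 0.3² = 27.9, so 28. The t-test version gives 29, and 29 / 0.955 for the efficiency of a rank test gives about 30. The stated 30 is reproduced.
- 30 / 0.5 = 60 per group. 60 / 0.9 = 66.7, so 67, which the plan rounds to 70.

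This calculation is for INR at admission. No sample size or power is given for delta-INR or fibrinogen.

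**2. SAP mixed model, response = delta.** Each patient has one value. The group coefficient is the between-arm difference in change, which is what is wanted. A pre/post time factor has no meaning, and a patient-level intercept cannot be separated from residual error.

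**3. SAP mixed model, response = the two INR values.** Without group-by-time, the group coefficient is the arm difference in each patient's mean of the two values. Randomization makes the expected prehospital difference zero, so a true arrival difference of 0.30 gives (0 + 0.30) / 2 = 0.15. A fitted random-intercept model on simulated data (1,000 per arm, true effect −0.30) gave −0.157 for group without the interaction, and −0.282 for group-by-time when it was included.

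**4. Power illustration.** From the documents: SD 0.4, effect 0.30, 60 per arm. Assumed: the same SD at both times, pre/post correlation ρ of 0.3 to 0.7, and the full 0.30 in all 60 patients per arm.

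- Group, no interaction: SE = √[(2/60) × 0.16 × (1 + ρ)/2]
- Group-by-time: SE = √[(2/60) × 2 × 0.16 × (1 − ρ)]
- ANCOVA: SE = √[(2/60) × 0.16 × (1 − ρ²)]
- Power = Φ(effect/SE − 1.96)

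| ρ | Group only (0.15) | Group-by-time (0.30) | ANCOVA (0.30) |
|---|---|---|---|
| 0.3 | SE 0.059, 72% | SE 0.086, 93% | SE 0.070, 99% |
| 0.5 | SE 0.063, 66% | SE 0.073, 98% | SE 0.063, 99.7% |
| 0.7 | SE 0.067, 61% | SE 0.057, 100% | SE 0.052, 100% |

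Simulation (1,000 trials per setting) gives 62-73%, 93-100% and 99-100%, which agrees within simulation error.

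**5. If only patients with coagulopathy benefit.** The plan sets 0.3 for the coagulopathic half. If the others gain nothing (an assumption), the average effect is 0.5 × 0.30 = 0.15. With SD unchanged and ρ = 0.5, power is Φ(0.075/0.0632 − 1.96) = 22% for group only, Φ(0.15/0.0730 − 1.96) = 54% for group-by-time and Φ(0.15/0.0632 − 1.96) = 66% for ANCOVA.

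**6. Paired t-test.** Suppose both arms rise by 0.1 and there is no arm difference (illustrated on the INR scale). At 60 per arm and ρ = 0.5 the change has SD 0.4, so SE = 0.4/√60 = 0.052 and each arm's paired test has power Φ(0.1/0.0516 − 1.96) = 49%. One arm is then significant and the other not in about 2 × 0.49 × 0.51 = 50% of trials. Simulation over 30 and 60 per arm and ρ of 0.3 to 0.7 gives 30-51%.

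**The case against.** A reader might infer that the plan cannot estimate either between-arm change. The documents do not support that. For fibrinogen, the SAP line with the paired t-test also names analysis of covariance, which estimates the baseline-adjusted arm difference. For delta-INR, the SAP says that delta values are compared between arms, and with delta as the response no interaction is needed. The intercept could be for centre, since SAP 16.7 wants centre effects considered, and time could mean elapsed time. The model would then be identifiable. Even a redundant patient intercept leaves the group contrast estimable. The logistic model is only in protocol 8.1, which defers to a separate analysis plan.

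These points stand, and they limit the criticism. They do not rescue the text. Centre and elapsed time are guesses, because the SAP states neither. Time with a random intercept is the usual form for repeated INR values, and protocol 8.1, which speaks of patient clustering, points the same way. Nothing gives the SAP precedence over 8.1.

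A reader might also infer that delta-INR will mix device and laboratory values. That goes too far: two sections say that the device measures both. The procedures and schedule do not show a device test at arrival, so this is a risk and an inconsistency, not an established fact. The study diagram in 3.3.4 was not available in the text examined and might bear on it.

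**Conclusion.** Wrong as written, for two secondary endpoints. Three things follow from the text alone: the sections name different methods; logistic regression does not fit a continuous delta with no cutoff; and a paired t-test does not compare arms. The SAP mixed model is either ill-defined in its time term and patient-level intercept (delta as response) or diluted to about half the effect (two INR values as response), depending on a choice the SAP does not state. It would be too strong to say that the plan estimates delta-INR at half its size, because that holds on one reading only.

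The halving on that reading follows from randomization and needs no assumed correlation. The power figures do depend on the assumed correlation, an equal SD at both times and 0.30 applying to all 60 per arm. They fall for every method if only patients with coagulopathy benefit. The primary Mann-Whitney comparison of arrival INR and its sample size are unaffected.

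**What to change.** In the synopsis, protocol 8.1 and SAP 16.7:

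- State the same model for each endpoint: ANCOVA of the arrival value on the prehospital value, keeping the planned ISS and centre terms. A two-time-point linear mixed model with a common baseline mean and a group-by-time term is an equivalent choice.
- Name the treatment coefficient (group in the ANCOVA, group-by-time in the mixed model) and its 95% CI as the reported estimate.
- Delete the logistic/GEE and paired t-test entries. Replace the synopsis comparison of admission fibrinogen medians, or label it descriptive.
- Reconcile protocol 3.1 and SAP 16.7 with protocol 3.3.1, 3.3.2 and 3.3.5 on how arrival INR is measured, and compute delta only from pairs measured by the same method (device with device, or laboratory with laboratory).

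The cost is wording in three places and no new data if paired venous samples are used. The downside is that protocol 3.3.1 asks for the prehospital venous sample only where possible. Some patients may lack a same-method pair and would rely on the planned multiple imputation, so the number of observed pairs per arm should be reported.

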| Treatments                                              | 
 
- FLYP (up to a maximum of 4 x 200 ml bottles)
 
- Normal saline (no limit required)
 
                                                                                                                                                                                                                                                                                                                                                                                                                                                                                                                                                                                                                                                                                                                                                                                         |
| Endpoints                                               | 
Primary Endpoint:
 
 
- INR at hospital arrival
 
 
Secondary Endpoints:
 
 
- INR-value variation between prehospital and in-hospital setting
 
- Collection of technical and logistical difficulties encountered before, during, and after the administration of FLYP.
 
- Variation in fibrinogen values between prehospital and hospital settings.
 
- Numbers of RBCs, platelet units, fibrinogen doses, clotting factors, plasma units needed during the first 24 and 48 hours
 
- Total length of stay in intensive care
 
- Number of days of hospitalization.
 
- 30-day survival rate.
 
                                                                                                                                                                        |

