#### **Data collected at the hospital after admission:**

- Results of blood group prior to administration of FLYP
- Results of biological samples for hemostasis analysis before and after administration of FLYP: PT, APTT, fibrinogen, CRP, coagulation factors
- Results of arterial blood gas: lactate, PaO2 (FiO2 noted), if performed
- Clinical parameters at intake (HR, BP, RR, SpO2, Temperature, Hemoglobin), time of collection
- Complete lesion assessment, time of assessment
- Severity score: ISS, IGSII, revised trauma score, TRISS
- Possible hemostasis surgery, administration of tranexamic acid, type of surgery, time of day
- Blood products transfused: name of the components transfused, time of administration
- Transfused blood derivatives: fibrinogen, ..., time of administration
- Evolution of amine requirements, administered syringe flow rate, administration time
- Evolution of hemostasis parameters
- Respiratory evolution: ventilation parameters (duration of mechanical ventilation, FiO2, etc.), ARDS-type complications
- Length of stay in Intensive care unit, mortality, date and time of death
- Length of stay, in-hospital, and 30-day mortality.

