#### **A comparison of key patient characteristics will be performed to validate the comparability of the two groups.**

This comparison will be made for the main variables of interest :

Age, sex, comorbidities, type of injury, mechanism of injury, anatomic localisation of trauma, time response of advanced life support teams, vital status at the point of injury (blood pressure, heart rate, shock-index, oxygen saturation), prehospital biological measures (Prothrombin time and INR value, Hemoglobin and lactic acid concentrations), body temperature, basic life support therapeutics, advanced life support therapeutics, cumulated crystalloid volume, cumulated plasma volume, prehospital red cell units transfused, vital signs on arrival at the intensive care unit (blood pressure, heart rate, shock-index, injury severity score, traumatic brain injury confirmed with CT scan, laboratory values - Hemoglobin, platelets, lactic acid, base excess)

The analysis will take into account a possible center effect

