## 1604 **16.3   Trial design**

- 1605
- 1606                   ▪   The trial is a Multicenter, randomized, open-label controlled study. From the prehospital phase,
- 1607                   the FLYP+ group receives the reference treatment, both symptomatic and etiological, as well as
- 1608                   the administration of FLYP. The control group (FLYP - group) receives the reference treatment,
- 1609                   both symptomatic and etiological, but no administration of FLYP, which is replaced by saline.
- 1610

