## 1799 **Harms**

- 1800                   ▪ The number of patients experiencing AE will be presented for each treatment arm.
- 1801                   ▪ For each patient, only the maximum severity experienced of each type of AE will be displayed.  
1802                   The number of occurrences of each AE will also be presented for each treatment arm. No  
1803                   statistical testing will be undertaken

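### Two of the four SAP safety components require a transfusion by name, so lung injury or overload after saline in an untransfused control patient does not enter the safety endpoint

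*Combined protocol and SAP*

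**What the plan says.** The SAP defines the safety endpoint as a composite: "Safety Endpoint is the occurrence of any of the following adverse events: thrombosis, allergic" "symptoms, transfusion-related acute lung injury, and transfusion-associated circulatory" overload. Under Analysis populations, safety is analysed in all randomized patients. The documents give no diagnostic criteria for the two transfusion-named events.

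SAP 16.3 describes the control arm as receiving reference treatment, "both symptomatic and etiological, but no administration of FLYP, which is replaced by saline". The protocol Summary sets no upper volume for that product: "Normal saline (no limit required").

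Both arms may also receive blood products that are not study treatment. Protocol 8.1 lists "prehospital red cell units transfused" among the characteristics described by group (SAP 16.6 repeats this), and it plans hospital use as an outcome: "The transfusion requirement will be compared by the number of blood products and plasma units transfused after arrival at the hospital". Neither document states what share of control patients is expected to be transfused.

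Outside the endpoint, the plan does capture neutral data. Protocol 7.2.1 asks investigators to record all adverse events in the CRF, and protocol 3.9 collects "Respiratory evolution: ventilation parameters (duration of mechanical ventilation, FiO2, etc.), ARDS-type complications". The SAP Harms section adds: "The number of patients experiencing AE will be presented for each treatment arm".

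On testing, the documents differ. The SAP says, for the safety endpoint and again under Harms, that no formal test is planned. Protocol 8.1 says adverse event incidence will be compared between the groups by a Chi2 or Fisher exact test.

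**The concern.** TRALI and TACO are attributions of a clinical event to a blood product. The underlying events, acute lung injury and fluid overload, can also follow trauma, shock or a large volume of saline. When such an event occurs in a patient who received FLYP, it can be labelled TRALI or TACO and counted. When it occurs in a control patient who received no blood product, no component fits it, so it is not counted in the composite.

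Two other parts of the protocol push the same way. The trial is open-label (3.8). Section 7.2.2 requires immediate notification of TACO but exempts complications secondary to hemorrhagic shock, so similar respiratory events could be filed under different headings in the two arms.

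At stake is the reading of the by-arm safety summary. SAP 16.2 has as an objective to validate the safety of prehospital plasma transfusion, and both documents express categorical effects as risk ratios with 95% confidence intervals. An excess in the FLYP column could arise from the component definitions alone.

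**Working it through.** **The plan's own figure.** There is none to reproduce: the documents give no expected rate, sample size or power for the safety endpoint. The only input taken from them is 70 patients per group (Summary). Everything else below is assumed.

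**Assumptions**
- q: true rate of lung injury or overload, the same in both arms (no product effect). Taken as 5%, 10% and 20%.
- t: share of control patients who receive any blood product, independent of event risk. Taken as 0.4 to 1.0.
- Every FLYP patient counts as transfused, and every lung or overload event in a transfused patient is labelled TRALI or TACO.

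**Step 1: the two transfusion-named components.** Expected count with FLYP = 70 × q. Expected count with saline = 70 × q × t. Apparent risk ratio = q / (q × t) = 1/t, whatever the value of q. The last column is the exact probability that a two-sided Fisher test at 5% would reject if it were applied to these two components alone.

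| q | t | FLYP | Control | Ratio | Fisher rejects |
|---|---|---|---|---|---|
| 5% | 0.4 | 3.5 | 1.4 | 2.5 | 4.2% |
| 5% | 0.8 | 3.5 | 2.8 | 1.25 | 1.5% |
| 10% | 0.4 | 7.0 | 2.8 | 2.5 | 17.0% |
| 10% | 0.6 | 7.0 | 4.2 | 1.67 | 7.6% |
| 10% | 0.8 | 7.0 | 5.6 | 1.25 | 3.6% |
| 10% | 1.0 | 7.0 | 7.0 | 1.0 | 2.5% |
| 20% | 0.4 | 14.0 | 5.6 | 2.5 | 45.6% |
| 20% | 0.8 | 14.0 | 11.2 | 1.25 | 6.4% |

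At t = 1 the rejection probability is 1.4% for q = 5% and 3.1% for q = 20%.

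**Step 2: the full composite.** Thrombosis and allergy do not require a transfusion and dilute the ratio. Suppose they add 7 non-overlapping patients per arm, with q = 10%:
- t = 0.4: (7 + 7) / (2.8 + 7) = 14 / 9.8 = 1.43
- t = 0.8: (7 + 7) / (5.6 + 7) = 14 / 12.6 = 1.11

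**Step 3: transfusion related to risk.** Let q1 be the event rate among transfused controls. The counted control rate is t × q1 and the ratio is q / (t × q1). If the sicker controls are the ones transfused, q1 exceeds q and the ratio is below 1/t. If all control events fall in transfused patients, t × q1 = q and the ratio is 1.0.

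**Step 4: arm-neutral components.** If lung injury and overload are counted whatever product was given, t drops out and the ratio is 1.0 under equal true rates.

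**The case against.** The best defence is that this is a list of plasma-specific events of interest, reported descriptively. The protocol itself names allergy and TACO as the plasma risks to watch (1.3, 7.2.2), the SAP plans no formal test, and an asymmetry of this kind would overstate plasma harm, not hide it. Saline-related lung injury or overload is still an adverse event under protocol 7.1.1, which does not require a causal link. It belongs in the Harms tables, and ARDS-type complications are collected in both arms. Labels do not rest on the treating team alone either, since the committee in protocol 7.5 rules on causality, although nothing says it is blinded to arm.

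Much of this stands. TRALI and TACO should stay in the report, and neutral data exist. What the defence does not remove is that those data do not feed the designated safety endpoint, and that the protocol, unlike the SAP, announces a between-arm test. That test is of adverse event incidence in general; neither document plans a test of the four-item composite by name.

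A reader might go further and infer that control patients can never score on these components, or cannot before hospital arrival. The documents do not support this: prehospital red cells and in-hospital products are recorded in both arms. Nor do they support a fixed doubling of the composite: the transfused share and the event rates are not given, and 1/t applies to two of the four components only.

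**Conclusion.** The point holds as an unequal definition within the safety endpoint. Control patients cannot have two of its four components from the study product and can score on them only after a non-study blood product. Under equal true rates and transfusion independent of risk, the apparent risk ratio for those two components is 1/t, or 2.5 to 1.25 for t between 0.4 and 0.8. It is smaller in the full composite (1.43 to 1.11 in the example above), smaller if sicker controls are the ones transfused, and 1.0 if all controls are transfused. These sizes rest on assumed q and t, on all FLYP patients counting as transfused, and on the event names, because no diagnostic criteria are given.

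It would be too strong to conclude that the plan cannot assess safety: adverse events by type and ARDS-type complications are available in both arms. The consequence is limited to how the by-arm safety summary is read. A correction is still worthwhile because that summary serves a stated SAP objective.

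**What to change.** In the SAP safety endpoint:
- Add two components defined by clinical event: any acute lung injury or ARDS-type complication, and any circulatory overload. State the criteria and apply the same window in both arms, regardless of the product given. Use these for the by-arm comparison.
- Keep TRALI and TACO as a descriptive haemovigilance classification of those events, without an arm comparison.
- Reconcile protocol 8.1 with the SAP (safety endpoint and Harms) on whether adverse events are tested between arms.

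The cost is SAP wording and additional table rows. ARDS-type complications are already in the CRF; overload may have to be classified from adverse event records. The downside is that more events caused by the injury itself enter the comparison in both arms, which can dilute a true product effect.
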